#### Sound Processing and Analyses

Each word will be excerpted from the continuous recording of each session to generate individual word audio files. Then, Praat and Matlab R2019b will be used to extract acoustic features as follows (Swain et al., 2018).

Prosodic features:

-Fundamental frequency, or pitch (Hz): mean and standard deviation over the entire waveform.-Speech rate: number of syllables per second.-Root mean square energy (Volts): square root of mean energy.-Intensity (dB): mean and standard deviation over the entire waveform.

Voice quality features:

-Jitter (%): it is an index of the periodic fluctuation of fundamental frequency. Average absolute difference between two consecutive periods, divided by the average period (jitter local). Average absolute difference between a period and the average of it and its four closest neighbors, divided by the average period (jitter ppq5).-Shimmer (%): it is an index of the periodic fluctuation of the signal amplitude. Average absolute difference between the amplitude of two consecutive periods, divided by the average amplitude (shimmer local). Average absolute difference between the amplitude of a period and its mean amplitude and its four closest neighbors, divided by the average amplitude (shimmer ppq5).-Mean harmonic-to-noise ratio (dB): mean ratio of the energy of the harmonics to the energy of the remaining part of the signal. It will be calculated as described by Eqs 1 and 2:

If 99% of the signal is composed of harmonics and 1% is noise, then:

(1)$$\text{Harmonic-to-noise ratio}=10\log_{10}\left(\frac{99}{1}\right)=20\text{dB}$$

Mean HNR between time point t1 and time point t2 is defined as:

(2)$$\text{Mean harmonic-to-noise ratio}=\frac{1}{\left(t_{2}-t_{1}\right)}\int_{t_{1}}^{t_{2}}dtx\left(t\right)$$

where *x*(*t*) is the harmonic-to-noise ratio (in dB) as a function of time.

Spectral features:

-Mean first, second and third formants (Hz): mean and bandwidth in center.-Mel Frequency Cepstral Coefficients: 1–13.

In order to reduce inter-individual biases due to physical anatomy (e.g., body corpulence), values from each parameter extracted will be rescaled between 0 and 1 according to the max-min normalization. The formula expressed in Eq. 3 will be used:

(3)$$x_{\text{normalized}}=\frac{x-\min_{kj}}{\max_{kj}-\min_{kj}}$$

Where *x* is the value to be normalized, *max*_*kj*_ is the highest value of acoustic feature *k* and *min*_*kj*_ is the lowest value of *k*.

For emotion comparisons, a one-way ANOVA will be applied on each acoustic feature and type of voice separately, excepting MFCC coefficients. Normality and homogeneity will be assessed using Shapiro–Wilk and Bartlett tests, respectively. In case of non-parametric distribution of the data, Kruskal–Wallis test will be applied. *Post hoc* tests will be used to statistically assess specific differences (Tukey after ANOVA, Wilcoxon tests with *p*-value adjustment by Holm method after Kruskal–Wallis).

To evaluate the effect of controlling frequency, familiarity, and concreteness, a Corpus (words selected from MADS versus words selected from INTERFACE) × Emotions ANOVA will be conducted on each acoustic features separately. Normality and homogeneity will be assessed using Shapiro–Wilk and Bartlett tests, respectively. In case of non-parametric distribution of the data, a transformation will be performed. *Post hoc* comparisons will be conducted to assess specific differences (Tukey).

For culture comparisons, previously mentioned features will be extracted also from INTERFACE database audio files for (1) Anger, (2) Disgust, (3) Fear, (4) Joy, (5) Neutral/normal, and (6) Sadness. Only the data from the INTERFACE word corpus found in the MESD will be considered to allow comparisons with the Castilian Spanish dataset. A repeated measures Cultures (Spanish vs Mexican) × Emotions ANOVA will be performed for each acoustic feature separately. Normality will be assessed by Shapiro–Wilk test. In case of non-parametric distribution of the data, a transformation will be applied. Mauchly’s test of sphericity will be used to evaluate homogeneity of variances and co-variances. In case of violation of sphericity, a Greenhouse-Geisser correction will be applied in order to test main effects significance. *Post hoc* comparisons will be conducted to assess specific differences (Tukey).

For all analysis, level of significance will be set at *p* < 0.05. Statistical analysis will be performed with R software.

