#### Sample

Four healthy male, four healthy female adults (between 19 and 35 years), and eight healthy children (between 9 and 11 years) (Stathopoulos et al., 2011) will voluntary participate to speech recordings. Participants will be excluded if they have been diagnosed with any pathology that affects emotional behavior, hearing, or speech, or present sickness traits affecting voice timbre at the time of the study. Participants will be included if they have grown up in Mexico in a cultural Mexican environment (Mexican academic education and family environments) in order to guarantee a Mexican-way of conveying emotions. Participants will be recruited from a public announcement posted on Tecnologico de Monterrey, Campus Monterrey.

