#### MESD Speech Corpus Stimuli

Words for speech utterances will be selected from two sources: the single-word corpus from the INTERFACE for Castilian Spanish database (Hozjan et al., 2002; Emotional Speech Synthesis Database, 2012), and the Madrid Affective Database for Spanish (MADS; Hinojosa et al., 2016a, b). For the creation of the MESD, the 24 isolated words that composed the INTERFACE database will be selected and will repeat across emotions. Words from MADS will be selected based on grammatical class and ratings for valence, arousal, qualitative emotion (anger, disgust, fear, happiness, neutral, and sadness), concreteness, familiarity, frequency, and subjective age of acquisition. Specifically, all words will be nouns or adjectives. Their subjective age of acquisition will be strictly under 9-year-old. Valence and arousal ratings of neutral words will be strictly greater than 4 but lower than 6 (on a 9-point scale), whereas emotional words will be selected to have valence and arousal ratings ranging from 1 to 4, or from 6 to 9. A rating superior to 2.5 (on a 5-point scale) for a particular emotion will allow the qualitative categorization of the word into anger, disgust, fear, happiness, or sadness. Words from MADS will be selected in order to ensure that they will be matched for concreteness, familiarity, and frequency ratings. Words selection will be carried out separately for male, female, and mean ratings for all subjects.

Statistical analysis will be used to guarantee that frequency, familiarity, and concreteness are matched between neutral, fear, disgust, happiness, sadness, and anger words. Values obtained for each of these parameters will be analyzed separately with one-way ANOVAs. Normality and homogeneity will be assessed using Shapiro–Wilk and Bartlett tests, respectively. In case of non-parametric distribution of the data, Kruskal–Wallis test will be applied. *Post hoc* tests will be used to statistically assess specific differences (Tukey after ANOVA, Wilcoxon tests with *p*-value adjustment by Holm method after Kruskal–Wallis). In case of significant differences between emotions, outlier values will be identified, and corresponding words will be eliminated until reaching no difference for all of three parameters. We will consider outliers all ratings for frequency, familiarity or concreteness outside the range defined by percentiles 2.5 and 97.5.

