Mean and standard deviation scores for male, female, children, and all together ratings will be calculated for each word. For culture comparisons, one-way ANOVAs will be conducted for each emotion and variable separately on words qualified as referring to a specific emotion in both cultures. Sample size estimation was calculated with G^∗^Power software version 3.1.9.7 (Faul et al., 2007) for Cohen’s d effect size index of 0.8, and statistical significance set at *p* < 0.05. Results indicated that 34 participants in each category (adult male, adult female, and child) would be enough to provide an estimated power of 0.90. For emotion comparisons in Mexican ratings, values obtained for each variable will be analyzed separately with one-way ANOVAs. Normality and homogeneity will be assessed using Shapiro–Wilk and Bartlett tests, respectively. In case of non-parametric distribution of the data, Kruskal–Wallis test will be applied. *Post hoc* tests will be used to statistically assess specific differences (Tukey after ANOVA, Wilcoxon tests with *p*-value adjustment by Holm method after Kruskal–Wallis). In case of cross-cultural differences, outlier values from both Spanish and Mexican ratings will be identified, and corresponding words will be eliminated until reaching no cultural difference, and no emotional difference for Mexican ratings for all of three parameters (familiarity, frequency, and concreteness). We will consider outliers all ratings for frequency, familiarity or concreteness outside the range defined by percentiles 2.5 and 97.5. The final speech corpus from MADS will be composed of 144 words (24 per emotion), so that the final MESD corpus will be composed of 48 words per emotion (24 from INTERFACE and 24 from MADS).

Forty Mexican participants of each category (adult male, adult female, and child) will voluntarily answer the questionnaires. Adults will be aged between 19 and 35 years old, and children between 9 and 11 years old. They will be excluded if they have been diagnosed with any pathology that affects emotional behavior. They will be included if that have grown up in Mexico in a cultural Mexican environment (Mexican academic education and family environments). Participants will be recruited via public posted on Tecnologico de Monterrey, Campus Monterrey.

In all cases, significance will be set at *p* < 0.05. Statistical analysis will be performed with R software (R Foundation for Statistical Computing, Vienna, Austria).

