#### Speech Recordings Elaboration and Procedures

Recordings will be carried out in a professional recording studio using the following material: (1) a Sennheiser e835 microphone, (2) a Focusrite Scarlett 2i4 audio interface connected to the microphone with an XLR cable and to the computer, and (3) the digital audio workstation REAPER (Rapid Environment for Audio Production, Engineering, and Recording) will be used to generate and record audio files that will be stored as a sequence of 24-bit with a sample rate 297 of 48000 Hz.

Sessions will last approximately 1 h for adults and 30 min for children. Adults will be asked to utter 288 words, that is 48 words per emotion, being 24 coming from INTERFACE, and 24 coming from MADS. Four children will utter the selected words from MADS (for a total of 144 words), and four children will express the words coming from INTERFACE (144 utterances). The order of word corpora will be counterbalanced across adult sessions, and emotions will be randomly distributed for both cases: adults and children. Participants will be asked to read and get grips with the entire word dataset and will be given as much time as they require. Then, they will be instructed to read each 24-word list with one of six emotional intonations: neutral, happy, angry, sad, disgusted, or afraid. Children who will express words coming from MADS will be presented with the corpora of words selected based on mean ratings for all subject. Adults male and female will utter words based on selection from mean ratings for males and females, respectively. Participants will be asked to do their best possible to get into the emotional role. All words from a particular emotion will be uttered successively to facilitate this process. Participants will be asked to wait at least 5 s between two utterances in order to focus before each recording.

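### The Stage 1 one-way ANOVA for acoustic emotion differences treats all utterances as independent although words repeat across emotions and speakers, so its 5% error rate does not hold

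*Protocol article*

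**What the plan says.** All places are in the protocol article, under Materials and Methods, Mexican Emotional Speech Database.

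- **Test.** Sound Processing and Analyses: "For emotion comparisons, a one-way ANOVA will be applied on each acoustic feature and type of voice separately, excepting MFCC coefficients". Kruskal-Wallis is the fallback, with Tukey or Holm-adjusted Wilcoxon tests post hoc. No word or speaker term is given.
- **Repeated words.** MESD Speech Corpus Stimuli: "the 24 isolated words that composed the INTERFACE database will be selected and will repeat across emotions".
- **Emotion-specific words.** Same section: "The final speech corpus from MADS will be composed of 144 words (24 per emotion"), hence "the final MESD corpus will be composed of 48 words per emotion (24 from INTERFACE and 24 from MADS").
- **Matching.** Same section: "Words from MADS will be selected in order to ensure that they will be matched for concreteness, familiarity, and frequency ratings". Vowels, phonemes and syllable structure are not mentioned.
- **Speakers.** Sample: "Four healthy male, four healthy female adults (between 19 and 35 years), and eight healthy children". Speech Recordings Elaboration and Procedures: "Adults will be asked to utter 288 words, that is 48 words per emotion, being 24 coming from INTERFACE, and 24 coming from MADS". Of the eight children, one half speaks the MADS words and the other half the INTERFACE words, so each word has four speakers in every voice type.
- **Related analyses.** Sound Processing and Analyses also plans a "Corpus (words selected from MADS versus words selected from INTERFACE) × Emotions ANOVA will be conducted on each acoustic features separately", and a repeated-measures Cultures × Emotions ANOVA restricted to the INTERFACE words.

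**The concern.** A one-way ANOVA is valid when the observations within and between emotions are independent. Here they are not, for two reasons that act in opposite directions.

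- The INTERFACE words are crossed with emotion. Their word-to-word differences cancel when emotions are compared, but the one-way test leaves them in the error term. That makes it too conservative.
- The MADS words are nested in emotion. If several speakers' recordings of the same word are pooled, those recordings share the word's acoustic character, but the test counts them as independent. That makes it too liberal.

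A separate issue concerns content. Formants, harmonics-to-noise ratio and intensity depend on which sounds are spoken. If the six MADS lists differ systematically in sound, that difference is indistinguishable from prosody in the MADS half.

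At stake is the Stage 1 description of which features separate the emotions. Stage 2 (Creation of Five Levels of Naturalness for Emotional Speech) refers back to these emotion orderings as relations to be preserved, and repeats the same kind of one-way test.

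**Working it through.** **1. The protocol's own figure.** Sound Processing and Analyses gives no power figure. Creation of Five Levels of Naturalness for Emotional Speech gives one for the same kind of test: d = 0.8, 19 words per emotion, power 0.92. With six emotions and f = d/2 = 0.4, the noncentrality is 0.4² × 114 = 18.24 on 5 and 108 degrees of freedom, and power is 0.916. The figure reproduces, on the assumption of independent words. The arithmetic is not at fault; the model is.

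**2. Inputs.** Six emotions, with 24 crossed and 24 nested words each; S utterances per word, with S = 1 (for example the final 288-utterance set) or S = 4 (all speakers of a voice type pooled); alpha 0.05. The share of variance due to the word, ρ, is not in the document and is assumed at 0.3, 0.5, 0.7 and 0.85. Total variance is 1 and no speaker effect is included.

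**3. Error rate.** The variance that matters when emotion means are compared is:

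- INTERFACE half: (1−ρ)/(24S), because the word effect cancels.
- MADS half: ρ/24 + (1−ρ)/(24S).

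An emotion mean is the average of the two halves, so the relevant variance is [2(1−ρ)/S + ρ]/96. The one-way ANOVA assumes 1/(48S). The ratio of true to assumed variance is

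(1−ρ) + Sρ/2 = 1 + ρ(S/2 − 1),

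which is 1 − ρ/2 for S = 1 and 1 + ρ for S = 4. Dividing the critical F by this ratio gives the approximate rejection rate under no effect. The critical values are 2.246 on 5 and 282 df (S = 1) and 2.222 on 5 and 1,146 df (S = 4).

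| ρ | S = 1: ratio | formula | simulated | S = 4: ratio | formula | simulated |
|---|---|---|---|---|---|---|
| 0.3 | 0.85 | 2.4% | 2.3% | 1.30 | 13.0% | 13.9% |
| 0.5 | 0.75 | 1.2% | 1.1% | 1.50 | 19.3% | 19.8% |
| 0.7 | 0.65 | 0.5% | 0.7% | 1.70 | 25.8% | 26.8% |
| 0.85 | 0.575 | 0.2% | 0.2% | 1.85 | 30.7% | 32.5% |

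The simulation used 8,000 data sets per cell. Across all runs made, the ranges are about 0.1-2.4% and 13-32%. The within-word test on the INTERFACE words stayed at about 5% throughout.

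**4. Power, one utterance per word.**

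| Effect | ρ | One-way, as planned | Word random effect |
|---|---|---|---|
| f = 0.15 | 0.5 | 0.37 | 0.65 |
| f = 0.20 | 0.5 | 0.72 | 0.91 |
| f = 0.231 | 0.5 | 0.87 | 0.975 |
| f = 0.4 | 0.2-0.8 | 1.00 | 1.00 |

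The word-term column treats the variances as known. The value f = 0.231 corresponds to d = 0.8 between only two of the six emotions. At f = 0.25 the planned test has power of about 0.91-0.94 for ρ from 0.3 to 0.85.

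**5. Systematic list differences, for illustration only.** Suppose prosody has no effect and the MADS list means differ with an assumed SD of 0.25 or 0.5 of the word SD (S = 1). For ρ from 0.5 to 0.85 the planned test rejects in about 8-10% and 40-59% of cases respectively. The document supports neither value.

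**The case against.** **The section already has checks.** A sound difference confined to the MADS lists would appear as an interaction in the Corpus × Emotions ANOVA, and the Cultures × Emotions ANOVA tests emotion on the repeated words. This stands in part, so it would be wrong to say that the repeated words are never analysed on their own. But the first analysis has no word term, is planned to evaluate control of frequency, familiarity and concreteness, and is not tied to the reading of the one-way result. For children, corpus is also confounded with speaker. The second does not name its repeated unit, and its emotion main effect averages over two cultures.

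**Real effects will not be missed.** At f = 0.4 this stands fully: power is about 1.00 with or without a word term. A reader might infer that the plan is underpowered for what it seeks; the document does not support that.

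**The list bias is assumed.** This also stands. A reader might take a false-positive rate of 40-59% as a property of the plan. It holds only for an assumed list difference of half a word SD, and a random word effect would not remove it, because MADS words are nested in emotion.

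**Downstream use is limited.** Largely right. The feature set comes from a literature review, the database is validated by classifier performance, and naturalness is defined from neutral voices. Speech rate is in syllables per second, which partly answers a concern about word length. The point concerns the inferential claim about emotion differences, not the construction of the database.

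**Conclusion.** The concern holds in a limited form. The one-way ANOVA does not fit the word and speaker structure that the protocol itself lays down, and its 5% level does not hold: about 0.1-2.4% with one utterance per word, and about 13-32% if four speakers are pooled. These ranges rest on an assumed word share of variance of 0.3-0.85 and on no speaker effect. The direction cannot be settled from the text, because the section does not say which utterances enter the test.

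Lost power is a matter for effects below f = 0.4 only. Confusion of word sound with prosody is possible because matching on sound is not stated, but its size is unknown and no rate should be attached to it. The correction is worth making because it is cheap and puts the test back near its stated level; it does not call the Stage 1 database into question.

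**What to change.** 1. State which utterances enter the emotion comparison: all speakers of a voice type, or one utterance per word.
2. For each feature and voice type, replace the one-way ANOVA by a mixed model with emotion fixed and word random (INTERFACE words crossed with emotion, MADS words nested in it). Add a speaker effect wherever several speakers are pooled.
3. Report the within-word emotion test on the 24 INTERFACE words as the estimate free of word-list differences. Run it on complete speaker recordings, because the final set may take different emotions from different speakers.
4. Report the MADS words separately, and say that list sound and prosody cannot be separated there.
5. Do not make agreement with the INTERFACE test a condition for calling a feature prosodic. That test uses half the words. At f = 0.25 and a word share of 0.3 its power is about 0.78, against about 0.92 for the planned pooled test.

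Cost: a change of analysis wording and slightly more analysis work, on the same recordings and features. The INTERFACE-only test has less power than the pooled test when the word share is low, which is why it is reported alongside the mixed model and not used as a gatekeeper.

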## Discussion

This project of investigation aims to fulfill three main gaps of the current scientific literature. First, acoustic parameters from Castilian and Mexican Spanish will be analyzed in order to validate a newly formed emotion speech database for Mexican Spanish and to highlight cross-cultural differences in the way of expressing emotions by prosody. The first issue was to determine which acoustic features should be considered to optimize the distinction from one emotion to another. As no reliable set of acoustic features exists yet, a literature review of prosodic emotional speech parameters was conducted. MFCC coefficients were the most usually extracted features for machine learning applications. This analysis consists of computing the log values of a linear cosine transform of spectral parameters on a Mel scale, thus considering the human particularities of frequency responses (Caballero-Morales, 2013). Other recurrent spectral features were the pitch (fundamental frequency), formants, jitter, shimmer and harmonics-to-noise ratio (Swain et al., 2018). Formants are high-energy frequencies acoustic resonances of the vocal tract (Gelfand, 2009). They are generally labeled F1, F2, F3, and so on, from the lowest formant to the highest: the first three- formants are usually extracted for emotions discrimination (Kamińska, 2019). Jitter and shimmer refer to a period-to-period fluctuation of the pitch and the energy, respectively (Arruti et al., 2014). The harmonics-to-noise ratio considers the energy of the harmonics according to the one of other frequencies. It is directly correlated to the voice quality according to breathiness and roughness and is a principal component to characterize human voices (Arruti et al., 2014). The energy, intensity and rate were other features commonly used for emotional prosody recognition (Swain et al., 2018). Therefore, it is suitable to extract those acoustic parameters for the present work and predict high accuracy in emotions discrimination and classification. However, previous studies have also highlighted the influence of linguistic parameters on emotions processing (Méndez-Bértolo et al., 2011; Palazova et al., 2011; Hinojosa et al., 2014). Therefore, it is necessary to supervise linguistic values, for all stimuli to be nouns and adjectives, valence, arousal, and emotional category to be in accordance with prosody, and frequency, concreteness, and familiarity matched between emotions, so that the unbiased allocation of prosody during recordings may be ensured. Controlling for these factors will add reliability to our database and enrich the current available material, as previous works for Spanish emotional utterances did not systematically control for linguistic features (Caballero-Morales, 2013; Hinojosa et al., 2016a, b; Pérez-Espinosa et al., 2020).

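### The Corpus × Emotions ANOVA cannot evaluate the effect of matching words on frequency, familiarity and concreteness, because the INTERFACE comparison words are already matched exactly across emotions

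*Protocol article*

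**What the plan says.** Under Sound Processing and Analyses, the article plans a two-factor ANOVA with this stated purpose: "To evaluate the effect of controlling frequency, familiarity, and concreteness, a Corpus (words selected from MADS versus words selected from INTERFACE) × Emotions ANOVA will be" carried out feature by feature.

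Under MESD Speech Corpus Stimuli, the two corpora are built differently:

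- INTERFACE: "the 24 isolated words that composed the INTERFACE database will be selected and will repeat across emotions".
- MADS: "Words from MADS will be selected in order to ensure that they will be matched for concreteness, familiarity, and frequency ratings". The aim of the check is explicit: "Statistical analysis will be used to guarantee that frequency, familiarity, and concreteness are matched between neutral, fear, disgust, happiness, sadness, and anger words". Words are removed until the tests show no difference.

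The Discussion gives control of the three ratings the same meaning: "frequency, concreteness, and familiarity matched between emotions".

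MADS words are also chosen on other grounds. These include emotional meaning ("A rating superior to 2.5 (on a 5-point scale) for a particular emotion will allow the qualitative categorization of the word into anger" or another emotion), valence, arousal, word class and age of acquisition ("Their subjective age of acquisition will be strictly under 9-year-old").

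Under Speech Recordings Elaboration and Procedures, each adult utters both corpora. Four children utter the MADS words and four other children utter the INTERFACE words.

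**The concern.** To evaluate the effect of controlling a word property, one arm must have the property controlled and the other must not. Here the arm that stands in for uncontrolled words is, on the article's own definition, the better controlled one. The two corpora differ in several other respects, and any of these could produce a Corpus effect or an interaction.

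What is at stake is interpretation. A significant result could be credited to the three ratings when something else caused it. A null could be read as showing that matching makes no difference. Neither conclusion would follow.

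**Working it through.** **Plan's own figures.** No sample size or power is stated for this ANOVA. The nearest figure is for the one-way word-matching ANOVA: 19 words per emotion, d = 0.8, power 0.92. With f = d/2 = 0.4, six groups and N = 6 × 19 = 114, the noncentrality is 0.4² × 114 = 18.24 on 5 and 108 df. The power is 0.916, so the figure reproduces, but it has no bearing on this point.

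**Step 1: matching in each corpus.** The recording section gives 144 INTERFACE utterances per child. 24 words × 6 emotions = 144, which confirms the repetition. For any word-level rating x, the mean in emotion e is (1/24)Σx over the same 24 words, so it is the same in every emotion. The between-emotion sum of squares, 24 × Σ(mean in e − overall mean)², is exactly 0.

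MADS has 24 different words per emotion. In one simulated draw (rating SD 1, same distribution in every emotion) the sum of squares was 1.42. With 5 df that is a mean square of 1.42/5 = 0.28 against a within-emotion variance of 1. Such a set would pass the matching test yet is not exactly balanced.

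**Step 2: what the ratings can contribute to the ANOVA.** Let b be the slope of an acoustic feature on a rating, taken as linear and common to all cells. Write M for MADS and I for INTERFACE.

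- Interaction, emotions e and e′: b × {[mean(M,e) − mean(M,e′)] − [mean(I,e) − mean(I,e′)]}. The second bracket is 0 and the first is pushed towards 0 by the word screening. Whatever the size of b, only chance imbalance in MADS is left.
- Corpus main effect: b × [mean(M) − mean(I)]. This is a difference in overall rating level between corpora, which is not the between-emotion control that the article describes.

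**Step 3: what else separates the corpora.**

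| Feature | MADS | INTERFACE |
|---|---|---|
| Words across emotions | different | same 24 repeated |
| Meaning agrees with prosody | by selection | cannot hold for one word in all six emotions |
| Valence, arousal, word class, age of acquisition | selected | no such selection stated |
| Child speakers | four children | four other children |

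**Step 4: illustration.** A 2 × 6 ANOVA with 24 words per cell was simulated 200 times per scenario. Emotion means were 0, 0.3, 0.6, 0.9, 0.4 and 0.2, residual SD was 1, and the three ratings had no effect. All effect sizes are assumptions.

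| Scenario | Corpus rejects | Interaction rejects |
|---|---|---|
| No effect of any kind | 4% | 4.5% |
| Emotion effects doubled on meaning-congruent MADS words | 93% | 38.5% |
| Speaker shift of 0.5 SD only (possible for children) | 98.5% | 3.5% |

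A second set of assumptions (emotion effects from −0.4 to 1.0 SD, word SD 0.5, residual SD 0.87, one speaker, 1,500 runs) gave interaction rejection in 7%, 25% and 89% for congruence boosts of 25%, 50% and 100%. The rates depend heavily on the assumptions. In both sets a result can be significant with no effect of the ratings.

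**Step 5: would covariate adjustment inside MADS recover the stated effect?** Assume a slope of 0.3 SD per rating for three independent ratings. In matched words, the difference between two emotion means of 24 words has SD √(2/24) = 0.289. The change in an emotion contrast on adjustment then has SD 0.3 × √3 × 0.289 = 0.15, centred on 0, and mean absolute size 0.15 × 0.798 = 0.12. In unmatched words running from −0.5 to +0.5 SD across emotions, the extreme contrast would move by 3 × 0.3 × 1.0 = 0.90 SD. Matching removes the very change that such a comparison would look for.

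**The case against.** The strongest defence is that control might be read more broadly. The Discussion says "Controlling for these factors will add reliability to our database and enrich the current available material", and the factors listed just before it include word class, valence, arousal and agreement of emotional category with prosody. On that reading MADS is the linguistically controlled corpus, and crediting a corpus difference to linguistic control in general is not plainly wrong. This stands for the Discussion. It does not rescue the ANOVA, whose purpose clause names only frequency, familiarity and concreteness.

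A second defence is that the corpora may differ in overall rating level and the Corpus main effect would pick this up. That is possible, but it is not matching between emotions, and it remains mixed with every other difference in Step 3.

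A third is that little depends on the result. This stands. Corpus size is fixed separately, speakers are selected by F-score, the database is validated by classification performance, and Stages 2 and 3 do not use this ANOVA. The article also states no rule for interpreting it.

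A reader might infer that the database, its validation or the claim made for it in the Discussion is undermined. The documents do not support that: those rest on word selection and classification, not on this test. Nor should the simulated percentages be taken as expected error rates. The congruence and speaker effects are assumed, and the article does not say how speakers enter the model.

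**Conclusion.** The stated purpose is wrong as written. INTERFACE is matched exactly across emotions and MADS approximately, so the ANOVA has no uncontrolled arm and cannot evaluate the effect it names. This follows from the design alone and needs no assumed effect size. The exact zero in Step 1 holds for any word-level rating; Step 2 assumes a common linear slope.

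For adult voices, the comparison is of emotion-congruent, distinct and otherwise selected words against repeated words. For child voices it is not even cleanly that. Corpus is confounded with speaker, and the interaction is confounded with how individual children express each emotion.

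The consequence is limited to what may be concluded from one secondary Stage 1 analysis.

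**What to change.** 1. Remove the purpose clause. Report Corpus × Emotions only as a description of emotion-congruent, distinct words versus repeated words, with no conclusion about frequency, familiarity or concreteness. For child voices, state that corpus and speaker are confounded.
2. If the influence of the three ratings is of interest, estimate it within the MADS words. For each acoustic feature, estimate the slopes on frequency, familiarity and concreteness within emotion, with word and speaker as random effects, and report them with confidence intervals.
3. Do not use the change in emotion contrasts after covariate adjustment as the measure. Step 5 shows that matching forces it towards zero even when the ratings matter, which would give another misleading null.

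Item 1 is a change of wording. Item 2 uses data already planned: the questionnaire ratings of familiarity and concreteness, and word frequency from LEXMEX. No recording or recruitment changes. The downside is precision: matching and outlier removal narrow the range of the ratings, so the slopes will have wide intervals, and a slope near zero should not be read as evidence of no effect.
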